#### Secondary Outcomes

For comparisons between secondary continuous outcomes and continuous outcomes, a linear regression with an identity function will be used. The secondary analysis of missing information will use the following two approaches to handle missingness: (1) imputation using the baseline observation carried forward or the classification of nonresponders as vapers in accordance with the Russell standard [35] and (2) imputation using the last observation of vaping status carried forward for nonresponders.

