*Crush the Crave* for vaping cessation was developed based on an earlier version of the app for smoking cessation [25-27]. An RCT of 1599 young adult smokers assessed *Crush the Crave* for smoking cessation and found that the 30-day point prevalence abstinence (PPA) at 6 months for the intervention condition (118/820, 14.4%) was not significantly different (odds ratio 0.82, 95% CI 0.63-1.08) from that for the control condition (132/779, 16.9%). However, the rate of abstinence was favorable when compared with the unassisted 30-day quit rates of 11.5% of young adults [28]. In addition, it was determined that 61% of the young adult smokers in the RCT were vaping. The increasing nicotine dependence and use of vapes among youth have prompted interest in developing an app for vaping cessation based on people’s experiences with *Crush the Crave* for smoking cessation. *Crush the Crave* is a tracker app that tracks the following information: the number of vape-free days and the amount of money saved since quitting vaping, as well as triggers and cravings. The app also provides the following functions: tailored supportive messages and inspirational graphic images for quitting vaping, personalized quit plans, graphic performance feedback, digital awards for achieving milestones, the reporting of vaping triggers, assistance for dealing with cravings, and links to other supportive resources that can aid in vaping cessation.

The primary aim of our study is to determine the effectiveness of the *Crush the Crave* app in supporting vaping cessation among youth recruited to the intervention arm via comparison with an assessment-only control group. The primary hypothesis is that participants in the intervention group—those using *Crush the Crave*—will be more likely to be abstinent at the 6-month follow-up point than participants in the assessment-only control arm. Our trial is currently open for recruitment. The anticipated completion date for our study is March 2024.

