### Recruitment and Enrollment

Eligible participants are youth aged 16 to 29 years who live in Canada and have used nicotine e-cigarettes in the previous 30 days. Study participants will be recruited through the Vaping Dependence Cohort—an existing panel of youth enrolled in a prospective cohort study at the University of Toronto who provided consent for recontact in future studies at the Ontario Tobacco Research Unit. This panel is comprised of a broad sample of youth who self-reported current or past regular use of nicotine e-cigarettes. The use of nicotine e-cigarettes was assessed through a question that asked respondents if they had used e-cigarettes daily, in the past week, in the past month, in the past 3 months, or in the past year and if they had ever used an e-cigarette. This cohort was designed to balance recruitment by smoking status (*ever* or *never*), e-cigarette use (*ever* or *never*), and age (16-18 years or 19-25 years). Consequently, the prevalence of smoking, e-cigarette use, and younger participants was higher than what would be expected in a simple random sample of the population. An analysis controlling for the study design elements found that the within-group characteristics of the included youth were broadly consistent with expectations, which were based on a representative sample [9].

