### Outcome Measures

The primary outcome variable will be self-reported 30-day PPA at 3 months, operationalized as not having vaped, even a puff, in the last 30 days. The secondary measures include the intention to quit smoking in the next 6 months (*yes* or *no*), number of puffs per vaping session, number of vape sessions per day, and number of sessions in the past 30 days.

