### Data Analysis Plan

#### Primary Outcome

Demographic and vaping characteristics (eg, vaping dependence, use of e-cigarettes, and self-confidence to quit) will be compared between groups at baseline. The intention-to-treat principle will be followed for statistical analyses, and all participants will be analyzed in the study arm to which they were randomized. Negative binomial regression with an identity function and robust SEs will be used to test between-group comparisons of the primary outcome variable—30-day PPA at follow-up. Multiple imputation via chained equations using the observed predictors of outcomes and the predictors of loss to follow-up will be performed to impute missing outcome data to correct for any potential bias caused by missing data. The imputation model will include age, sex and gender, education, marital status, province of residence, ethnicity, vaping dependence, self-confidence to quit, perceived stress, and the intervention group. The inverse of the adjusted risk difference will provide the number needed to treat.

The sample size of 600 (inclusive of both the control arm and the intervention arm) was selected to differentiate an effect size odds ratio of 1.60, assuming a base cessation rate of 5%, an α of .05, a power of 0.8, and a 75% (450/600) response rate.

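### A secondary outcome asks about quitting smoking in a vaping-cessation trial, and the only secondary-outcome model sentence gives this yes/no item no method

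*Protocol article*

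**What the plan says.** The Introduction gives the aim: to "determine the effectiveness of the *Crush the Crave* app in supporting vaping cessation among youth". Under Recruitment and Enrollment, participants must "have used nicotine e-cigarettes in the previous 30 days"; current smoking is not an entry condition. Of the source panel the same section says "This cohort was designed to balance recruitment by smoking status" (ever or never), so the panel contains never-smokers.

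Under Outcome Measures, the primary outcome is abstinence from vaping over 30 days. Then: "The secondary measures include the intention to quit smoking in the next 6 months", answered yes or no. The remaining named measures are "number of puffs per vaping session, number of vape sessions per day, and number of sessions in the past 30 days".

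Under Secondary Outcomes in the Data Analysis Plan, one sentence assigns a model: "For comparisons between secondary continuous outcomes and continuous outcomes, a linear regression with an identity function will be used". The other methods in the plan belong elsewhere. The Primary Outcome section says "Negative binomial regression with an identity function and robust SEs will be used to test between-group comparisons of the primary outcome variable", and the chi-square test under Process Analysis is for process measures.

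**The concern.** There are two defects in the text, and both concern the same item.

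First, the intention item names a different behaviour from the one the app targets. A participant who has never smoked cannot give a meaningful answer, and a participant who vapes and smokes could answer yes without any intention to stop vaping. Followed literally, the trial would have no intention measure for vaping among its named secondary outcomes, and an effect of the app on readiness to quit vaping could go unseen.

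Second, the model sentence repeats one outcome type where a second type was presumably meant. The yes/no item is left without an analysis, so the effect measure, the test and the handling of people who have already quit could all be chosen after the data are seen.

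Two smaller matters arise from the same list. Puffs per session has no value for a person with no sessions, which includes every participant who meets the primary outcome. And the vaping-quantity outcomes can be analysed more precisely at no cost if their baseline values are used.

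**Working it through.** **1. Which behaviour does each part of the protocol address?**

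| Element | Section | Behaviour |
|---|---|---|
| Aim and hypothesis | Introduction | vaping |
| Eligibility | Recruitment and Enrollment | nicotine e-cigarette use |
| Primary outcome | Outcome Measures | vaping |
| Three quantity outcomes | Outcome Measures | vaping |
| Intention item | Outcome Measures | smoking |

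The intention item is the only one that departs.

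**2. To how many participants could the item apply?** The sample-size paragraph expects 600 × 0.75 = 450 responders. If a share s of them does not smoke, the item applies to 450 × (1 − s). The protocol does not give s. As an assumed range: s = 10% leaves 405, s = 50% leaves 225, s = 90% leaves 45. Nothing in the document narrows this range.

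**3. Is any stated method available for a yes/no secondary outcome?** Linear regression is stated for continuous outcomes, negative binomial regression for the primary outcome, and chi-square for process measures. None is assigned to this item.

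**4. Does linear regression fail for the three counts?** The expected number per arm is 450 / 2 = 225. The document gives no mean, SD or distribution for the counts, so the distributions here are assumed: negative binomial with mean 10, dispersion k = 0.3, 0.5 and 1, and 5% extra zeros (skewness about 3.7, 2.9 and 2.0), with 10,000 simulated trials each.
- Type I error of the linear comparison: 4.8%, 5.1% and 5.0%.
- Coverage of the 95% interval for the mean difference, with and without an effect: 94.8% to 95.2%.

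The linear comparison of arm means is valid under these assumptions. In a separate log-scale scenario (225 per arm, 26% fewer sessions, log SD 1.0, 7% zeros), unadjusted power was 65.6% for linear and 66.6% for negative binomial regression. Changing the model alone gains about 1 point.

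**5. What does baseline adjustment add?** In that scenario, with an assumed log-scale baseline correlation of 0.6, linear regression rose from 65.6% to 74.1%; a second simulation gave 66% to 76%. A closed-form check agrees. In units of the squared median:
- Baseline variance: e² − e = 7.389 − 2.718 = 4.671.
- Follow-up variance with 7% zeros: 0.93 × 7.389 − 0.93² × 2.718 = 4.521.
- Covariance: 0.93 × 2.718 × (e^0.6 − 1) = 0.93 × 2.718 × 0.822 = 2.078.
- Raw-scale correlation: 2.078 / √(4.671 × 4.521) = 0.452, so the standard error shrinks by √(1 − 0.452²) = 0.892.
- Power of 65.6% corresponds to a signal of 1.96 + 0.40 = 2.36 standard errors. Then 2.36 / 0.892 = 2.65, and Φ(2.65 − 1.96) ≈ 75%.

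**6. Who has no value for puffs per session?** Anyone abstinent for 30 days has no sessions in that period. The plan's own inputs, 5% and an odds ratio of 1.60, give odds of 1.60 × 0.05/0.95 = 0.0842 and so 0.0842/1.0842 = 7.8%. Per 225 responders that is about 11 control and 17 intervention participants. With the 8% and 16% that the Discussion reports for the earlier text-messaging trial, it is 18 and 36. The Primary Outcome section says all participants are analysed as randomised, so these people need a defined value or the outcome needs a different role.

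**The case against.** The strongest reply is that this is a condensed article: smoking is a slip for vaping carried over from the earlier smoking version of the app, and the binary method sits in a fuller plan. That may be so. But the model sentence is not merely short. It names the same outcome type twice and so is defective as it stands. A slip that changes a named outcome still has to be corrected or confirmed. One could also argue that intention to quit smoking is a deliberate spillover measure in people who do both; the document states no such purpose.

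A reader might go further and infer that linear regression is the wrong model for the counts, or that the count model and the normal model were assigned to each other's outcomes. The documents support neither. The skew is an assumption, and linear regression kept its error rate and coverage in the simulations above. The identity function for the primary outcome has a stated purpose, a risk difference and a number needed to treat.

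Nor does the panel's balance on smoking fix the share of never-smokers in the trial. The panel was also balanced on e-cigarette use, and the trial takes only recent nicotine vapers from it.

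On baseline adjustment, the Secondary Outcomes section is silent rather than contrary, and covariates may be left to a fuller plan. On puffs per session, nothing says that quitters will be dropped, so a comparison of post-randomisation subsets is a risk and not a stated analysis. Both are therefore improvements offered alongside the main point.

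**Conclusion.** The point holds for the intention item. It names smoking where the aim, eligibility and primary outcome concern vaping, and no stated method covers it. This affects one of the four named secondary measures. It leaves the primary outcome untouched but would make the item uninformative about the app's target. The conclusion rests on the text alone. The size of the inapplicable group cannot be given, because the share of participants who do not smoke is not stated.

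Baseline adjustment is a free gain, about 8 to 10 points of power in one assumed scenario (log SD 1.0, correlation 0.6), and smaller if the correlation is weaker. Puffs per session is undefined for abstainers: about 11 and 17 per arm on the plan's own rates, more if abstinence is higher.

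Linear regression for the counts is acceptable at about 225 per arm. A baseline-adjusted count model with robust standard errors is an optional efficiency choice. It changes the estimand to a ratio, and its gain depends on distributions that the document does not give.

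**What to change.** - **Intention item.** Change it to intention to quit vaping in the next 6 months, or confirm that smoking is a slip and that the fielded questionnaire already asks about vaping. Give participants who have already quit their own level, or group them as quit or intending versus neither.
- **Model sentence.** Remove the repetition and name a binary method for this item, such as logistic regression with a standardised risk difference.
- **Vaping quantities.** Adjust each for its baseline value and count abstainers as 0 sessions. Data Collection already covers e-cigarette use at baseline, and the planned baseline carry-forward presupposes such values.
- **Puffs per session.** Report it descriptively among continuing vapers, or replace it with puffs per day with abstainers as 0.

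The cost is wording, plus at most one questionnaire item if intention to quit vaping is not already asked; the baseline survey covers cessation goals. Recruitment began in March 2022, so the sponsor should first check which wording has been fielded. Answers already given about smoking cannot be recoded as answers about vaping.

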### Randomization

Eligible participants will be identified from the Vaping Dependence Cohort. The *rand()* function in Excel (Microsoft Corporation) allowed for simple randomization; the top 50% highest numbers identified the participants that will receive invitations to use the *Crush the Crave* app. A research assistant from the Vaping Dependence Cohort will conduct the randomization and create a variable with a blinded key for the initial data analysis, which will allow the investigators and analyst to be blinded to the group allocation up until the data analysis is complete.

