### Data Collection

A baseline questionnaire will be sent to both the intervention group and the control group, using a self-administered web-based survey. This will collect comprehensive data on the history and characteristics of vaping (eg, vaping dependence, use of e-cigarettes, and self-confidence to quit), self-perceived addiction to vaping, health status (including mental health, mood, and perceived stress), and current and previous history of the use of other substances (combustible cigarettes, marijuana, alcohol, hookahs, and other tobacco products). The baseline survey will also ask questions on environmental factors and cessation goals. Self-reported demographic data (age, sex, gender and sexual orientation, province and country of residence, race and ethnicity, education, and marital status) will also be collected in the baseline survey.

A follow-up survey will be sent to the control and intervention groups at 3, 6, 9, and 12 months. Responses to the follow-up survey will be used to analyze any significant changes in vaping habits and differences between groups. The follow-up survey questionnaire includes items on cross-contamination and the use of cessation methods.

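### The linear model for the secondary vaping-quantity outcomes has no stated baseline term; adding each outcome's own baseline value would gain precision at almost no cost

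*Protocol article*

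**What the plan says.** The Outcome Measures section lists three quantities among the secondary measures: "number of puffs per vaping session, number of vape sessions per day, and number of sessions in the past 30 days".

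Their analysis is given in one sentence of the Secondary Outcomes section: "For comparisons between secondary continuous outcomes and continuous outcomes, a linear regression with an identity function will be used". It names a model family and a link. It names no covariate and excludes none.

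Four other places bear on the point:

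- **Data Collection**, on the baseline survey: "This will collect comprehensive data on the history and characteristics of vaping (eg, vaping dependence, use of e-cigarettes, and self-confidence to quit". The three quantities are not named individually. The same section says that follow-up responses will be used to look at change in vaping as well as at differences between arms.
- **Secondary Outcomes**, on missing data: one approach is "imputation using the baseline observation carried forward or the classification of nonresponders as vapers"; the other carries forward the last vaping status.
- **Randomization**: the random-number "function in Excel (Microsoft Corporation) allowed for simple randomization". No stratification is stated.
- **Primary Outcome**: "The inverse of the adjusted risk difference will provide the number needed to treat". The covariates behind that adjustment are not listed. The imputation model there does have an itemised list. It includes vaping dependence but none of the three quantities.

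**The concern.** Anyone who used a nicotine e-cigarette in the previous 30 days is eligible, so daily and occasional users can enter together and starting quantities may differ widely. If a person's later quantity tracks the earlier one, part of the spread at follow-up was already present at baseline. A model without the baseline value leaves that spread in the residual variance.

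Under simple randomization without stratification, the arms can also differ by chance in starting level, and an unadjusted contrast carries part of that difference into the estimate. The article plans to compare baseline characteristics between arms but does not say what follows for these outcomes if they differ. Stating the adjustment in advance removes a choice that could otherwise be made after the data are seen.

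The article's text is also not quite aligned: Data Collection speaks of analysing change, while the model sentence in Secondary Outcomes contains no starting value.

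**Working it through.** **The plan's own figure.** The article gives no sample size, standard deviation or power for the quantity outcomes, so there is nothing to reproduce for them. The sample size of 600 is justified for the abstinence outcome only and has no bearing here, except that it supplies the expected number of responders.

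**Inputs.**

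- Responders: 75% of 600 = 450, or 225 per arm at 1:1 (Primary Outcome; Trial Design).
- Two-sided alpha 0.05 and power 0.80. The article gives 0.05 without stating sidedness; two-sided is assumed.
- Correlation rho between baseline and follow-up: not in the documents. Assumed, from 0.1 to 0.7.
- Outcomes are expressed in SD units, with equal SD at baseline and follow-up.

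**Step 1: precision.** Unadjusted, the standard error of the arm difference is sqrt(2/225) = 0.094 SD. With the baseline value as a covariate it is multiplied by sqrt(1 - rho²). The variance saving is therefore rho², and the equivalent unadjusted sample is 450/(1 - rho²). The difference detectable with 80% power is (1.960 + 0.842) × 0.0943 × sqrt(1 - rho²), which is 0.264 SD without adjustment.

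| Assumed rho | Variance saving | SE ratio | Equivalent unadjusted N | Detectable difference (SD) | Power for 0.264 SD |
|---|---|---|---|---|---|
| 0 (no gain) | 0% | 1.000 | 450 | 0.264 | 80% |
| 0.1 | 1% | 0.995 | 455 | 0.263 | 80.4% |
| 0.3 | 9% | 0.954 | 495 | 0.252 | 83.6% |
| 0.5 | 25% | 0.866 | 600 | 0.229 | 89.9% |
| 0.7 | 49% | 0.714 | 882 | 0.189 | 97.5% |

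At rho 0.5, for example, 450/(1 - 0.25) = 600: adjustment would offset, in precision, the planned 25% non-response.

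**Step 2: chance imbalance.** With 225 per arm, the baseline difference between arms has standard error 0.094 SD, so its 95% range is ±1.96 × 0.0943 = ±0.185 SD. The probability of an imbalance above 0.1 SD in either direction is 2 × (1 - Φ(0.1/0.0943)) = 29%. An imbalance of 0.1 SD moves the unadjusted estimate by rho × 0.1, which is 0.03, 0.05 and 0.07 SD at rho 0.3, 0.5 and 0.7.

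**Step 3: are the baseline values there?** Three statements point to yes: the baseline survey covers use of e-cigarettes, change in vaping is to be analysed, and baseline observations are to be carried forward. None names puffs or sessions. The carried-forward wording stands beside a rule on classifying people as vapers and could refer to vaping status alone. Availability is a strong inference, not a stated fact.

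**The case against.** The strongest reply is that one sentence in a condensed article is being asked to do too much. It gives a model family and is silent on covariates, and covariate lists for secondary models are commonly left to an analysis plan, which is not shown. The mention of an adjusted risk difference for the primary outcome, also without its covariates, suggests that the article abbreviates adjustment rather than rejects it. The intention to analyse change suggests the same. This stands. A reader might infer that the trial has chosen to compare follow-up on arm alone; the text does not say so.

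A second reply is that the unadjusted contrast is not wrong. Randomization keeps it unbiased over repetitions, and its standard error already allows for chance imbalance. This also stands: what is lost is precision, and correction for the imbalance that actually occurs.

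A third is that the gain is assumed. That is right as to its size: it is negligible at a correlation of 0.2 or less (a variance saving of at most 4%), and zeros among those who quit may pull the correlation down. A reader might infer that much of the information in these outcomes is being wasted; without a correlation in the documents, that cannot be said.

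A reader might also infer that follow-up at 3, 6, 9 and 12 months obliges a repeated-measures model. It does not. A regression at one time point is valid, and the article does not say that these outcomes will be tested at every wave.

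What survives is that the stated model lacks a term that is probably available and costs one degree of freedom.

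**Conclusion.** The point holds as an inexpensive improvement of low severity, confined to the secondary quantity outcomes. The article states their comparison without a baseline term, although its other statements imply that the baseline values exist and that change is of interest. The saving in variance runs from 1% at a correlation of 0.1 to 49% at 0.7, with 25% at 0.5. The conclusion rests on three assumptions: that the baseline survey records the three quantities, that the correlation lies somewhere in this range, and that no analysis plan already specifies the adjustment. Neither the validity of the comparison nor the primary outcome is in question here.

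**What to change.** Add one sentence to the Secondary Outcomes section: each secondary quantity outcome is analysed with its own baseline value as a covariate, provided the baseline survey records that quantity. If an analysis plan already says this, the article's wording need only be aligned with it. The sentence also brings the model into line with the stated aim of analysing change.

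The cost is one sentence and one degree of freedom per model. No new data are needed if the baseline survey holds the three quantities, which the sponsor should confirm.

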**Objective:**

The primary aim of our study is to determine the effectiveness of the *Crush the Crave* app in supporting vaping cessation among youth recruited to the intervention arm via comparison with an assessment-only control group. The primary hypothesis is that participants in the intervention group—those using *Crush the Crave*—will be more likely to be abstinent at the 6-month follow-up point than participants in the assessment-only control arm.

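### Carrying the last vaping status forward is a weak sensitivity analysis for 30-day abstinence: redundant at 3 months, and biased in an unknown direction after that

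*Protocol article*

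**What the plan says.** All references are to the protocol article.

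- **Endpoint (Outcome Measures).** Abstinence means "not having vaped, even a puff, in the last 30 days".
- **Entry (Recruitment and Enrollment).** Eligible participants "have used nicotine e-cigarettes in the previous 30 days", so nobody is 30-day abstinent at baseline.
- **Waves (Data Collection).** "A follow-up survey will be sent to the control and intervention groups at 3, 6, 9, and 12 months".
- **Main handling of missing outcomes (Primary Outcome).** "Multiple imputation via chained equations using the observed predictors of outcomes and the predictors of loss to follow-up will be performed to impute missing outcome" values.
- **Sensitivity analyses (Secondary Outcomes).** "The secondary analysis of missing information will use the following two approaches to handle missingness". The first is "imputation using the baseline observation carried forward or the classification of nonresponders as vapers in accordance with the Russell standard". The second is "imputation using the last observation of vaping status carried forward for nonresponders". Since the second refers to vaping status, it is read here as applying to abstinence.
- **Time point.** Outcome Measures sets the primary outcome at 3 months. The Objective says that app users "will be more likely to be abstinent at the 6-month follow-up point". That conflict is a separate matter, but it decides which half of the point below bears on the primary result.

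**The concern.** The endpoint describes the 30 days before a survey. If the survey is missing, carry-forward fills that window with the answer from an earlier one. From a 3-month response, the substituted answer is 3, 6 or 9 months old at the 6-, 9- and 12-month surveys. Someone abstinent at 3 months who then stops responding counts as abstinent for the rest of the trial. Someone vaping at 3 months who later quits without responding counts as a vaper.

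The two secondary approaches are the only check the article states on the assumption behind the primary imputation, and the plan expects a quarter of outcomes to be missing. If one check repeats the other, or moves the result in a direction nobody can predict, its agreement with the primary analysis gives little reassurance and its disagreement cannot be interpreted.

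**Working it through.** The plan gives no figure for this analysis, so there is none to reproduce. The check has three parts.

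**1. At 3 months.** No follow-up wave precedes 3 months, so a 3-month nonresponder's last observation is baseline. Everyone vaped at baseline, so carry-forward assigns vaping. Baseline carried forward and nonresponder = vaper assign the same value. All the stated rules give one result, and the two approaches are a single scenario.

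**2. At 6 months, illustration.** The 25% nonresponse follows from the plan's 75% response rate, which is not split by arm or wave. The other inputs are assumptions: 3-month abstinence *a* of 12% (app) and 8% (control), relapse of one half by 6 months in both arms, no late quitting, and nonresponse unrelated to outcome within arm. Let *d* be nonresponse at 6 months and *q* the share of 6-month nonresponders who answered at 3 months. The rest have only baseline to carry and count as vapers.

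- True 6-month rate: p = a × (1 − 0.5), so 6% vs 4%, a difference of 2.0 points.
- Carry-forward rate: (1 − d) × p + d × q × a.
- q = 1: 0.75×6 + 0.25×12 = 7.5%; 0.75×4 + 0.25×8 = 5.0%. Difference 2.5 points.
- q = 0.5: 0.75×6 + 0.125×12 = 6.0%; 0.75×4 + 0.125×8 = 4.0%. Difference 2.0 points, no bias.
- In general the difference is 1.5 + q points, so with q below one half carry-forward understates the effect.
- If instead all nonresponders who had quit early have relapsed, the truth is 0.75×6 = 4.5% vs 0.75×4 = 3.0%, or 1.5 points. Carry-forward then overstates it for any q above 0.

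**3. Direction when the arms differ.** Here 3-month abstinence uses the plan's planning values: 5% in control, and odds ratio 1.60 gives (1.6×0.05/0.95)/(1 + 1.6×0.05/0.95) = 7.77% for the app. Relapse, late quitting and nonresponse by arm are assumptions, with q = 1. The bias in the risk difference is

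d_app × (a_app − p_app) − d_ctl × (a_ctl − p_ctl).

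| Scenario (app / control) | True RD | Carry-forward RD | Nonresponder = vaper RD |
|---|---|---|---|
| Nonresponse 25/25%, relapse 40/40% | 1.66 | 1.94 | 1.25 |
| Nonresponse 35/15%, relapse 40/40% | 1.66 | 2.45 | 0.48 |
| Nonresponse 15/35%, relapse 40/40% | 1.66 | 1.43 | 2.01 |
| Nonresponse 25/25%, relapse 50/30% | 0.38 | 0.98 | 0.29 |
| Nonresponse 25/25%, relapse 30/50% | 2.94 | 2.89 | 2.20 |
| Nonresponse 25/25%, relapse 40/40%, late quitting 5/3% | 3.42 | 3.26 | 2.57 |

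Risk differences are in percentage points. For the third row: 0.15×(7.77−4.66) − 0.35×(5−3) = 0.47 − 0.70 = −0.23, and 1.66 − 0.23 = 1.43. With no true effect (5% in both arms, 40% relapse) the bias is (d_app − d_ctl) × 2.0 points. That is zero with equal nonresponse, +0.40 at 35/15% and −0.40 at 15/35%.

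**Precision.** At 75% response, 150 of 600 outcomes would be filled and treated as observed. With the same variance per participant, standard errors computed on 600 rather than 450 are smaller by the factor √(450/600) = 0.87, about 13%.

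**The case against.** A reader might infer that carry-forward inflates the app effect and so leans towards the hypothesis at 6 months. The documents do not support that. The rule applies to both arms, and the article gives no relapse rate, no late-quit rate and no nonresponse by arm or wave. The scenarios above go both ways. The 2.5 against 2.0 also requires every 6-month nonresponder to have answered at 3 months, and the excess is gone if half did not.

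Other points for the plan:

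- **Size.** In the illustration the excess of 0.5 points is 1.5 participants per arm of 300, and the risk ratio is 1.50 under both carry-forward and truth. This stands, although the plan works on the risk-difference scale and inverts it for the number needed to treat: 1/0.025 = 40 against 1/0.020 = 50.
- **Bracketing.** With q = 1 in the illustration, nonresponder = vaper (1.5) and carry-forward (2.5) enclose the true 2.0. This is not general. In the last two rows of the table the truth lies above both analyses, and at 3 months there is no bracket at all.
- **Role.** Multiple imputation is primary and these analyses are labelled secondary. This stands and limits the severity.
- **Filled values treated as known.** The same is true of nonresponder = vaper, which is worth keeping. So this is not a reason on its own to prefer one rule over the other. Nonresponder = vaper is useful because it is a declared extreme.
- **Unseen analysis plan.** The absence of a tipping-point analysis from an article is not a fault, since the full plan may contain one. The point here rests on a rule that the article does state.

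**Conclusion.** The point holds as a minor one. At 3 months the carry-forward analysis adds nothing, and this follows from the eligibility rule and the survey schedule without further assumption. At 6, 9 and 12 months it can misstate the risk difference in either direction, depending on relapse, late quitting and the pattern of nonresponse in each arm. Under the illustration's assumptions the error at 6 months runs from none (half of the 6-month nonresponders also missed 3 months) to 0.5 points (none did). Under the arm-specific assumptions tabulated, it runs from −0.23 to +0.79 points. These sizes rest on assumed rates and show what is possible, not what to expect. The primary conclusion does not rest on this analysis.

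**What to change.** For abstinence, replace the carry-forward analysis in Secondary Outcomes with a modified multiple imputation. Take the primary imputation model, multiply the odds of abstinence in nonresponders by a factor from 1 down to 0, vary the factor separately in the two arms, and report the values at which the conclusion changes. A factor of 1 in both arms is the primary analysis, and a factor of 0 in both arms is nonresponder = vaper. The range therefore links the two analyses the plan already has and shows what lies between them. Keep nonresponder = vaper as the anchor.

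The change needs no new data and no change to the design. It costs a sentence or two of analysis wording, a short extra program, and a table in the report instead of one number.
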